#### Formal Stopping Rules

The trial may be terminated early for overwhelming efficacy if the interim test statistic crosses the prespecified O’Brien-Fleming boundary (corresponding to a one-sided significance level of 0.0026), or for futility based on conditional power assessment, as determined by the Independent Data Monitoring Committee.

### Participants Research Protection

While there is a certain risk of information leakage, we have implemented comprehensive measures to mitigate such risks. EDC system is secured via username and password authentication, with all patient information being encrypted to ensure that only authorized research personnel and regulatory officials can access participant data. Individuals will be identified solely by a unique ID number and initials in all data analyses and publications.

Following the trial, participants who demonstrate a positive response to the investigational product may choose to continue its use at their own discretion. For those with a suboptimal response, other appropriate therapeutic options will be recommended based on their specific clinical presentation.

Additionally, should any participant sustain harm during the trial that is medically determined to be related to the study, the sponsor will provide appropriate compensation.

### Dissemination Plans

The findings of this study may be submitted for publication in peer-reviewed medical journals, conference presentations, broadcast media, and presentations to stakeholders. In all publications, participant confidentiality will be strictly protected in accordance with applicable laws and regulations. No personally identifiable information will be disclosed unless mandated by law.

### Ethical Considerations

This study will be conducted in accordance with the principles of the Declaration of Helsinki and relevant Chinese laws, regulations, and guidelines pertaining to clinical trials. The study protocol has been approved by the Ethics Committee of Shanghai Hospital of Traditional Chinese Medicine (Approval ID: 2024SHL-KY-108‐02). Any protocol amendments must be submitted to the lead Ethics Committee for approval. Once approved, they shall then be submitted to the ethics committees of all participating sites for filing. After having fully understood the trial’s methodology, objectives, potential benefits, and risks, all eligible participants will provide signed informed consent in person, agreeing to the collection of trial-related subject data and biological specimens.

## Results

This study is designed to enroll a total of 316 participants. Participant enrollment is set to commence in October 2025, with no recruitment having occurred as of April 2026. The recruitment period will extend until September 2028 or until the target enrollment is met. Data analysis is scheduled for November 2028, with submission of the trial results to a peer-reviewed journal anticipated by May 2029.

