## Methods

### Trial Design

This study uses a randomized, double-blind, active-controlled (low-dose control), prospective, multicenter design. Eligible participants will be randomized in a 1:1 ratio to either the intervention group or the control group. Prior to enrollment, baseline data—including medical history, physical examination findings, relevant laboratory results, and patient-reported outcomes—will be collected for screening and eligibility confirmation. All enrolled participants will be managed under a unified protocol. The combined drug and psychological intervention will be administered over a 3-month period. On completion of the intervention, participants will undergo 3 subsequent follow-up visits, each spaced 3 months apart, resulting in a total follow-up duration of 12 months. Figure 1 presents the participant flow through the trial.

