### Blinding

This study adopts a double-blind design. Drug blinding and distribution packaging are jointly carried out by statisticians who are not directly involved in this clinical trial and the pharmaceutical factory responsible for drug production. The trial drug and the control drug are respectively assigned unique drug packaging numbers and drug blinding codes, which are filled in (or pasted) on the drug labels. The control drug contains 10% of the components of the investigational drug. This active-controlled design provides a more rigorous comparison and addresses the practical challenges of producing an indistinguishable placebo in TCM research.

An independent blind background file will be established for each random number. The content includes key information such as the group to which the subject with the number is assigned (such as group A or group B) and the medication requirements (investigational drug or control drug) in case of emergency unblinding. The third party responsible for the random system is responsible for confidential storage. It is only opened by authorized personnel in accordance with the procedures in emergency situations, such as SAE, where unblinding is necessary.

A 2-step unblinding method will be adopted. After all research data are entered, verified, and have undergone blinded review, the database will be locked. The first unblinding will be performed by the blinding code custodian to identify group A and group B. This information will then be handed over to the biostatistician for statistical analysis. After the statistical analysis is completed, the second unblinding will be conducted to clarify the intervention and control groups.

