### Follow-Up

During the 3-month treatment period, follow-up visits will be scheduled once per month. After the completion of treatment, follow-up assessments will be performed every 3 months. The total follow-up duration will be 1 year. Data collection time points are presented in Table 2.

**Table 2. T2:** Study timeline.

Study stage	Screening and baseline period	Treatment period			Follow-up period		
Visit (times)	0	1	2	3	4	5	6
Time point (day)	−14 to 0	30	60	90	180	270	360
Time window (day)	+3 or −3	+3 or −3	+3 or −3	+3 or −3	+7 or −7	+7 or −7	+7 or −7
Collection of basic medical history							
Informed consent	✓						
Emission standards	✓						
Demographic data	✓						
Diagnosis and treatment history	✓						
Assessments of validity							
MDASI-OC^a^ scale	✓	✓	✓	✓	✓	✓	✓
PSQI^b^ sleep scale	✓	✓	✓	✓	✓	✓	✓
PFS-R^c^ scale	✓	✓	✓	✓	✓	✓	✓
PHQ-9^d^ depression scale	✓	✓	✓	✓	✓	✓	✓
GAD-7^e^ anxiety scale	✓	✓	✓	✓	✓	✓	✓
EORTC QOL-C30^f^ scale	✓	✓	✓	✓	✓	✓	✓
TCM^g^ syndrome scale	✓	✓	✓	✓	✓	✓	✓
One-year OS^h^ rate and PFS^i^ rate							✓
Sleep quality	✓	✓	✓	✓			
Sleep diary	✓	✓	✓	✓			
fMRI^j^	✓			✓			
Biological targets in peripheral blood	✓			✓			
Biological targets in tumor tissue	✓						
Tumor markers	✓			✓			
Proportions of immune cells	✓			✓			
Cytokine levels	✓			✓			
HPA^k^ axis function	✓			✓			
Analysis of immune gene expression	✓			✓			
Vital signs	✓	✓	✓	✓	✓	✓	✓
Laboratory Test Indicators and ECG^l^	✓			✓			
AE^m^ and SAE^n^	✓	✓	✓	✓	✓	✓	✓

a MDASI-OC: MD Anderson Symptom Inventory for Ovarian Cancer.

b PSQI: Pittsburgh Sleep Quality Index.

c PFS-R: Piper Fatigue Scale-Revised.

d PHQ-9: Patient Health Questionnaire-9.

e GAD-7: Generalized Anxiety Disorder-7.

f EORTC QOL-C30: European Organisation for Research and Treatment of Cancer Quality of Life Questionnaire - Core.

g TCM: traditional Chinese medicine.

h OS: overall survival.

i PFS: progression-free survival.

j fMRI: functional magnetic resonance imaging.

k HPA: hypothalamic-pituitary-adrenal.

l ECG: electrocardiography.

m AE: adverse event.

n SAE: serious adverse event.

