#### Primary Outcome Analysis

The primary end point is the PNSC remission rate at 3 months after enrollment. The chi-square test will be used to analyze whether the difference in remission rates between the two groups is statistically significant. Meanwhile, the difference in remission rates between the experimental group and the control group, along with the 95% CI, will be calculated. In addition, to account for potential between-group heterogeneity, a binary logistic regression model will be performed, with group as the main independent variable and baseline PNSC scores included as covariates. Study center will be included as a fixed effect to account for potential between-center heterogeneity. In addition, longitudinal PNSC scores will be analyzed using the methods described below for repeated continuous outcomes.

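### If recruitment runs to its September 2028 limit, the November 2028 analysis precedes complete 12-month follow-up and, by a narrow margin, the last 3-month primary visits

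*Protocol article*

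**What the plan says.** The calendar stands in the Results section and is repeated in the Abstract.

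- Start and status: "Participant enrollment is set to commence in October 2025, with no recruitment having occurred as of April 2026".
- End of recruitment: "The recruitment period will extend until September 2028 or until the target enrollment is met".
- Analysis and publication: "Data analysis is scheduled for November 2028, with submission of the trial results to a peer-reviewed journal anticipated by May 2029".

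The follow-up is set elsewhere.

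- Trial Design describes three quarterly visits after the 3-month treatment, "resulting in a total follow-up duration of 12 months".
- Table 2 (Follow-Up) lists the visit days as "14 to 0 30 60 90 180 270 360", with windows of 3 days either side up to day 90 and 7 days either side after that.
- Primary Outcome Analysis: "The primary end point is the PNSC remission rate at 3 months after enrollment".
- Survival Period bases the one-year OS and PFS rates on a year of follow-up from randomization. Table 2 also schedules the symptom and quality-of-life scales at days 180, 270 and 360.

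The condition for analysis is in Blinding: "After all research data are entered, verified, and have undergone blinded review, the database will be locked". Unblinding and the statistical analysis come after that lock. The only earlier look is one interim analysis, when about half of the participants have their 3-month assessment.

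**The concern.** Two months separate the latest permitted enrolment from the planned analysis, but the primary endpoint needs three months and the full follow-up needs twelve. If recruitment uses the time allowed, the lock rule and the analysis date cannot both be kept.

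If the lock rule governs, the published analysis and submission dates will be missed by most of a year. If the date governs, the analysis runs on incomplete data. A large minority of participants would have no 12-month scales and less than one year of survival follow-up, and a few would have no primary outcome. The document does not say which would give way.

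**Working it through.** **Inputs.** Recruitment limit September 2028, analysis November 2028, submission by May 2029, planned start October 2025 and none recruited as of April 2026 (Results); day 90 and day 360 with their windows (Table 2); target 316 (Sample Size). Exact days within a month are not given, so both ends of the month are used.

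**Step 1: last visits if recruitment runs through September 2028** (enrolment date + 90 or + 360 days).

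| Enrolled | Day 90 (window) | Day 360 (window) |
|---|---|---|
| 1 Sep 2028 | 30 Nov 2028 (27 Nov to 3 Dec) | 27 Aug 2029 (20 Aug to 3 Sep) |
| 30 Sep 2028 | 29 Dec 2028 (26 Dec to 1 Jan 2029) | 25 Sep 2029 (18 Sep to 2 Oct) |

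The stated November 2028 date therefore cannot be reproduced from the stated follow-up. From November 2028 to September 2029 is 10 months; from May to September 2029 is 4 months.

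**Step 2: how early enrolment would have to close** (milestone date minus 90 or 360 days).

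- Day 90 complete: 1 Nov 2028 − 90 d = 3 Aug 2028; 30 Nov 2028 − 90 d = 1 Sep 2028. The early edge of the window adds 3 days.
- Day 360 complete: 1 Nov 2028 − 360 d = 7 Nov 2027; 30 Nov 2028 − 360 d = 6 Dec 2027. The early edge of the window adds 7 days.
- Day 360 complete by the end of the submission month: 31 May 2029 − 360 d = 5 Jun 2028.

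**Step 3: participants affected.** The article gives no accrual curve. The assumption here is even accrual of 316 up to 30 September 2028. The number incomplete is 316 × (days from the Step 2 cut-off to 30 Sep 2028) / (days of accrual). Accrual lasts 1,095 days from 1 Oct 2025 or 883 days from 1 May 2026. The days after the cut-off are 58 or 29 for day 90, and 328 or 299 for day 360, for analysis on 1 or 30 November.

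| Start | Analysis | No day 90 | No day 360 |
|---|---|---|---|
| 1 Oct 2025 | 1 Nov 2028 | 316 × 58/1,095 = 16.7 | 316 × 328/1,095 = 94.7 (30%) |
| 1 Oct 2025 | 30 Nov 2028 | 316 × 29/1,095 = 8.4 | 316 × 299/1,095 = 86.3 (27%) |
| 1 May 2026 | 1 Nov 2028 | 316 × 58/883 = 20.8 | 316 × 328/883 = 117.4 (37%) |
| 1 May 2026 | 30 Nov 2028 | 316 × 29/883 = 10.4 | 316 × 299/883 = 107.0 (34%) |

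The October 2025 rows are a lower bound, because the article reports no recruitment as of April 2026.

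**The case against.** September 2028 is an outer limit, since recruitment also ends once the target is met. The dates are forecasts in a journal article, and no test, sample size or visit schedule depends on them. The lock rule in Blinding is a real safeguard: applied as written, it would delay the analysis and not let it run on partial data. All of this stands. It limits the consequences but does not reconcile the dates. Early closure saves the 12-month data only if it comes by about November or early December 2027, which the article does not state and which recruitment not having begun by April 2026 makes less likely. For the primary endpoint the objection is stronger, because closing by about August 2028 is enough.

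A reader might infer more than the document supports:

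- *That the end dates were left alone after a late start.* No earlier timetable is shown, so this cannot be known.
- *That a re-estimated sample size could not fit.* The cap of twice 316 is 632. Over the 29 months from May 2026 to September 2028 that is 21.8 a month, or 3.6 per centre across 6 centres. The article gives no accrual capacity, so impossibility is not shown.
- *That multiple imputation would fill visits not yet due.* It is planned for missing follow-up data and attrition; nothing extends it to visits still in the future.
- *That one-year OS and PFS would be invalid.* Kaplan-Meier, log-rank and Cox methods accommodate administrative censoring. The loss is mainly one of precision and follow-up.
- *That follow-up in progress would certainly be unmasked.* The first unblinding step gives the biostatistician only A and B labels, and nothing says that codes go to sites or participants. The risk arises only if the second step follows an early analysis.

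**Conclusion.** The calendar is wrong as written: recruitment to September 2028, 12 months of follow-up, lock after all data and analysis in November 2028 cannot all hold. The 12-month mismatch is the main problem, at about 10 months for the last participant and about 86 to 117 participants (27% to 37%). The 3-month gap is real but narrow, at about 8 to 21 participants. The dates follow from the article alone. The counts rest on even accrual to 30 September 2028 and a start between October 2025 and May 2026. Both gaps depend on recruitment using most of its permitted period, which is allowed but not certain. The November date cannot be read as a planned 3-month primary analysis, because none is described, and participants enrolled later in September 2028 would still lack day 90.

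**What to change.** Reconcile the dates in the Abstract and Results with the follow-up and the lock rule, by one of these routes:

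1. Move the final lock and analysis to after the last 12-month visit, which means about October 2029 or later if recruitment ends in September 2028, with submission after that.
2. Keep November 2028 and state an earlier close of recruitment, by about early November to early December 2027.
3. Prespecify two locks. The first is a 3-month primary lock after the last day-90 visit and its window, from January 2029 if recruitment runs to the limit. The second is a 12-month lock for OS, PFS and the long-term scales. Allocation is withheld from sites and participants until the second lock.

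The cost is a few corrected dates, or one paragraph for the two-lock option. Under routes 1 and 3 the full report comes up to about a year later. Route 2 compresses recruitment instead.

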## Discussion

This study is a multicenter, randomized, double-blind clinical trial with a low-dose positive control, and it will enroll 316 patients with ovarian cancer and PNSCs. The aim is to test the effect of the TSZA regimen on the symptom cluster of fatigue, insomnia, anxiety, and depression. The study also follows survival and measures inflammatory factors, immune function, neuroimaging, and multiomics to confirm its clinical value and explore its biological mechanism.

As noted earlier, the high rate of PNSC in patients with ovarian cancer is not due to one factor but results from surgery, chemotherapy, psychological stress, lack of social support, and uncertain prognosis. These factors form a complex stress network and trigger a cascade of symptoms [35]. Studi

es show that chronic stress keeps the HPA axis active and disrupts secretion rhythms [36]. This long-term imbalance is a biological basis of PNSC, and it also reduces natural killer cell activity and increases proinflammatory cytokines, which creates an immune-suppressive environment that supports tumor growth and spread [37]. For example, basic research shows that chronic stress increases glucocorticoids and disrupts neutrophil circadian rhythm and promotes neutrophil extracellular traps, which helps build a premetastatic environment [38]. Clinical data also show that patients with anxiety or depression have shorter PFS [39]. This study focuses exactly on key points of the psychoneuroimmune axis.

The unique advantage of the TSZA regimen is that it combines herbal treatment with psychological intervention. The main components of Compound Ciwujia Granules, such as eleutheroside, have been shown to regulate the HPA axis and increase brain-derived neurotrophic factor, so they improve cognitive function and emotional stability at the molecular level [40-42]. In addition, a single intervention is not enough to deal with complex cancer-related symptom clusters. For symptom clusters with emotional and cognitive problems, the effect of drug treatment is often limited. Given that standard psychological interventions such as CBT have strong evidence in oncology [43], they are integrated into our protocol to optimize therapeutic outcomes. This approach uses cognitive adjustment to rebuild coping strategies and improve psychological resilience, and it works together with Compound Ciwujia Granules to form a combined internal and external treatment model.

A key innovation of this study is the use of advanced methods to link TCM with modern science. In addition to treating the clinical symptoms of PNSC in ovarian cancer, this study also explores the biological mechanism of the TSZA regimen. We use fMRI to observe changes in functional connectivity in the limbic system, including the amygdala and hippocampus, to provide imaging evidence of symptom improvement and to show its effect on central neural circuits. We also test peripheral blood and tumor tissue to identify biomarkers related to PNSC relief at the molecular level. This approach combines macroscopic imaging and molecular data and supports the scientific basis of integrated TCM in managing cancer symptom clusters.

With the evolving understanding of the cancer symptom spectrum, symptom management is shifting from traditional supportive care to a key component influencing treatment outcomes [44]. PNSC not only impairs quality of life but also indirectly compromises antitumor efficacy by reducing treatment adherence and chemotherapy completion rates. In this context, this study can be regarded as an intervention targeting systemic anticancer therapy through a PNSC-based approach, rather than merely symptomatic management. We propose that alleviation of PNSC may be achieved by reducing systemic inflammatory burden, modulating the neuroendocrine-immune axis, and enhancing resilience to psychological stress. This approach may provide biological plausibility for the symptom-inflammation-immunity-tumor control continuum. Furthermore, the protocol follows the core idea of holistic oncology by integrating symptom management with antitumor therapy to optimize both survival and quality of life.

This study has several limitations. First, owing to technical difficulties in preparing a placebo for herbal medicine, a low-dose active comparator (containing 10% of the active components) is used instead. Although the control intervention is well matched to the investigational treatment in appearance, smell, and taste, it may retain partial pharmacological activity, potentially leading to an underestimation of the true treatment effect. Second, the generalizability of the findings from this study is somewhat limited. The study population is restricted to mainland Chinese patients with ovarian cancer who meet the TCM syndrome diagnosis of spleen-kidney yang deficiency. To ensure internal validity and robust causal inference, patients with a history of psychiatric disorders will be excluded. This measure aims to minimize confounding factors, ensuring that the observed PNSC is predominantly attributable to the malignancy and its treatment rather than a continuation of preexisting conditions. Furthermore, from an ethical and clinical safety perspective, patients with established psychiatric disorders require specialized care that exceeds the scope of this supportive intervention. While these criteria may limit the generalizability of the findings, they prioritize participant safety and the integrity of the study data. Third, the primary and most secondary end points are based on patient-reported outcomes; in the context of concomitant psychological interventions, response bias and performance effects cannot be fully excluded. Fourth, mechanistic exploratory analyses, including fMRI and multiomics, are conducted in a randomly selected subset, which may limit statistical power. Finally, although the 12-month follow-up is sufficient to assess symptom improvement, it may be inadequate to evaluate long-term OS.

In summary, the burden of psychological symptoms plays a critical role in tumor initiation, progression, and prognosis, underscoring the need for proactive psychoneurological symptom interventions in clinical practice. This study aims to provide high-quality evidence for the comprehensive management of PNSCs in patients with ovarian cancer. We anticipate that this study will not only improve the clinical manifestations of PNSCs and enhance patients’ quality of life but also strengthen antitumor immune responses and synergistically improve the efficacy of standard therapies, ultimately contributing to prolonged survival. In addition, the TSZA regimen, which integrates TCM with modern psychological interventions, may have broader applicability across other cancer types. This approach is expected to facilitate the integration of the biopsychosocial model into contemporary oncology and provide a practical framework for developing multidimensional intervention strategies.
